### Procedure for unblinding if needed {17b}

As this study includes two exercise-based interventions with clear modification guidelines related to the participants’ symptom response, emergency unblinding is not relevant. Instead, in case of serious adverse events reported by participants or treating physiotherapists, participants will be referred to their general practitioner, as is the normal procedure in Denmark, and encouraged by the project manager to explain the type and intensity of exercises they have performed.

## Data collection and management

### Plans for assessment and collection of outcomes {18a}

Before starting data collection, the outcome assessors will receive comprehensive education by the principal investigator in the assessment protocol over two sessions, to agree on standardised procedures for all objective outcome measurements. For all participants, data collection will be performed at baseline and at the 16-week follow-up on self-reported outcomes and objective measurements, and at the 12-month follow-up on self-reported outcomes via email as a secure online link (Fig. 2). Participants will complete the self-reported measurements directly into REDCap, and outcome assessors will enter the data in REDCap from their clinical tests and objective examinations at completion of those assessments. Data collection will be performed in an undisturbed room. At supervised exercise sessions, the treating physiotherapists will register the data concerning the exercise session (pain level, load, progressions, repetitions, sets, adverse events, and pain level before and after the session) in a printed exercise logbook, and at home-based sessions, the participants will fill out the exercise logbook. Data from the weekly questionnaire are entered by the participants directly into REDCap. All forms were designed by the Steering Committee.

### Plans to promote participant retention and complete follow-up {18b}

In REDCap, an automatic report has been created to monitor whether the participants answer the weekly questionnaire. For non-responders, an email reminder will be sent out twice with a 1-day interval, and if not answered on the third day, the project manager will contact the participants by phone. Two weeks before the planned 16-week follow-up testing, the project manager will contact the outcome assessor and the participant to make sure that an appointment has been scheduled. The project manager will collect the exercise logbooks regularly as participants complete the 16-week exercise programme.

### Data management {19}

REDCap will be the data collecting and storage system to accomplish the legislative requirements about management and safekeeping of data. A pre-defined codebook is developed, and data will be entered directly into REDCap with validation rules where relevant to verify data entered in a record that meets the specified standards. The principal investigator BL, together with [name], will have personal access to data by a confidential login to REDCap. An epidemiologist will get access to pseudo-anonymous data in SharePoint or OneDrive. In the “cleaning” process of raw data in preparation for the analysis, the “cleaning” procedures will be saved as a do-file (statistical commands) and data will be saved in a new file to keep the raw data file available. In the process of producing new variables, distribution characteristics of the new variable will be scrutinised and compared with the source and target variable to check for correctness of calculations. A project logbook will be created to be able to keep an overview of management procedures for the data. During data cleaning, data will be checked for duplicates, and summarised data and tabulated data will be used to identify missing data, outliers, and errors. A research assistant outside the project will type in data from the exercise logbooks.

### Confidentiality {27}

All personal information about potential and enrolled patients will be collected and saved in REDCap, which complies with international recommendations for confidential data protection. Medical information about participants in the study will be confidential, and disclosure to third parties other than the Steering Committee (BL, [name], [name], JS, and KS) will be prohibited. With the participant’s permission, medical information may be shared with his or her personal general practitioner or with other medical personnel responsible for the participant’s care. Data will be de-identified when exported from REDCap. When publishing data from this study, the presentation format will not include names, recognisable photos, personal information, or other data, which may disclose the identity of participants. We will also suppress cell sizes less than three.

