### Adverse event reporting and harms {22}

Adverse events will be defined as any unintended, negative findings, symptom, or illnesses that occur during the study assessments or interventions, whether attributable to the project or not. Minor adverse events cover symptom flare up, subluxations, and exercise-induced fatigue. Serious adverse events are unexpected but cover life-threatening events, disability, and permanent damage [69]. Adverse events are recorded at every exercise session in the exercise logbook and in the weekly questionnaire. The treating physiotherapists are familiar with the modification guidelines to reduce the exercise load, if participants experience short-lasting minor adverse events. Acute increase in shoulder symptoms, such as severe shoulder pain (e.g. 8 or higher on the NPRS), including pain during rest or more shoulder subluxations or dislocations than usual, will be reported to the project manager by participants and/or treating physiotherapists. As a safety precaution, if a medical evaluation is indicated, the participants will be referred to their general practitioner, which is the normal procedure in Denmark. Serious adverse events will be reported to the Regional Committee on Health Research Ethics for Southern Denmark within 7 days after the principal investigator or others from the Steering Committee have become aware of the incident without being unblinded. Serious adverse events will be assessed by health professionals outside the project for possible connection with the assessment and/or intervention in the project, but all adverse events will be reported irrespective of their relationship with assessment or intervention. In case of acute injury during the project assessment or intervention, the participants will be able to seek compensation from The Danish Patient Compensations Association and/or by making a complaint to The National Agency for Patients’ Rights and Complaints. We will report both the number of patients experiencing minor adverse events and serious adverse events as well as the number of minor adverse events and serious adverse events during the interventions.

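### The unqualified rule to suppress published cells below three conflicts with the promise to report adverse event counts, and dislocations are assigned to neither reported class

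*Protocol article*

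**What the plan says.** **Suppression rule.** Confidentiality {27} sets the format for publication: "When publishing data from this study, the presentation format will not include names, recognisable photos, personal information, or other data" that could identify a participant. The next sentence is "We will also suppress cell sizes less than three". It does not say which tables it covers and exempts none.

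**Harms commitment.** Adverse event reporting and harms {22} states "We will report both the number of patients experiencing minor adverse events and serious adverse events", and adds the number of events in each of the two classes. It also says that "all adverse events will be reported irrespective of their relationship with assessment or intervention".

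**The two classes.** For the minor class: "Minor adverse events cover symptom flare up, subluxations, and exercise-induced fatigue". For the serious class: "Serious adverse events are unexpected but cover life-threatening events, disability, and permanent damage".

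**Events named outside the classes.** The same section gives severe shoulder pain, with a rating of 8 or more as its example, as an acute increase in symptoms. This, or "more shoulder subluxations or dislocations than usual, will be reported to the project manager". The section does not say in which class either kind of event is counted.

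**The concern.** Both statements govern the same published harms table. A cell with one or two affected patients must be shown under the harms section and withheld under the confidentiality section. Small cells are most likely for serious events, which the protocol itself does not expect, in arms of about 50.

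This matters more here than in many trials. Background and rationale {6a} says that clinicians hold back from heavy loading because they are unsure it is safe, and the safety evidence it cites for the programme is a feasibility study of 12 patients. No data-monitoring committee and no interim analysis are planned. Harm counts by arm are therefore what outside readers will use to judge tolerability.

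The classification point is separate. Recurrent atraumatic dislocation is one of the manifestations that can qualify a patient for the trial, so further dislocations are foreseeable. With no class assigned, they could be counted as minor, as serious or under neither heading, and that choice could be made after the data are seen.

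**Working it through.** **1. Denominator.** Sample size {14} gives a difference of 252 points, an SD of change of 350, two-sided alpha of 0.05 and 90% power.
- Normal approximation: n = 2 × (1.960 + 1.282)² × (350/252)² = 2 × 10.51 × 1.929 ≈ 40.5, so 41 per group.
- The t-based calculation gives 42 (power 0.903), which is the protocol's figure.
- Allowing for 16% dropout: 42/0.84 = 50 per group, as stated.
- The recruitment stopping rule permits 76 patients in total, or 38 per group.

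The planned sizes reproduce, so arms of 38 to 50 are the right denominators.

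**2. Probability that a count is masked.** The documents give no harm rates, so the per-patient risk p is an assumption and a range is shown. For n patients in an arm:
- P(0) = (1 − p)ⁿ
- P(1 or 2) = n·p·(1 − p)ⁿ⁻¹ + [n(n − 1)/2]·p²·(1 − p)ⁿ⁻²
- P(masked, given at least one affected) = P(1 or 2) / [1 − P(0)]

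Worked case, n = 50 and p = 0.02: P(0) = 0.364; P(1 or 2) = 0.557; ratio = 0.557/0.636 = 0.88.

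| Assumed risk | n = 50: P(0) | n = 50: P(1 or 2) | n = 50: masked if non-zero | n = 38: masked if non-zero |
|---|---|---|---|---|
| 1% | 0.605 | 0.381 | 0.97 | 0.98 |
| 2% | 0.364 | 0.557 | 0.88 | 0.93 |
| 4% | 0.130 | 0.547 | 0.63 | 0.75 |
| 5% | 0.077 | 0.464 | 0.50 | 0.66 |
| 10% | 0.005 | 0.107 | 0.11 | 0.24 |

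These are counts of patients for one harm in one arm. Counts of events can be larger, because one patient may have several.

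**3. What a masked cell withholds.** Read literally, below three includes zero, so 0, 1 and 2 of 50 would look alike. Their exact 95% upper limits are 7.1%, 10.6% and 13.7%.

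**4. Classes set side by side.**

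| Event | Named as minor | Named as serious | Meets the general adverse event definition |
|---|---|---|---|
| Subluxation | Yes | No | Yes |
| Dislocation | No | No | Yes |
| Acute severe pain | Not by name; could be a symptom flare-up | No | Yes |

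Only dislocation is clearly without a named class.

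**The case against.** **The rule is disclosure control.** It stands under Confidentiality, directly after a sentence about identifying participants, and does not mention harms. The harms section is the more specific commitment, and a statistical analysis plan, not shown here, may settle how tables are built. This stands in part: the authors may never have meant to mask harms. But the rule is written without limits and the article gives no order of precedence, so the conflict is in the stated text and is not a detail left out.

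**Dislocations and severe pain would still be reported.** A reader might infer that both would go unpublished. The documents do not support that. The adverse event definition is broad, events are recorded at each session and in the weekly questionnaire, and all are to be reported whatever their relationship to the intervention. The class descriptions may also be illustrative. This stands: the events are captured, and the gap is in classification. It is firm only for dislocations.

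**The consequence is limited.** A reader might also infer that suppression would leave the trial unable to say anything on safety. That goes too far. A masked cell still shows that at most two patients were affected, common harms stay visible, and a split of 2/50 against 0/50 has a two-sided Fisher p of about 0.49. A trial of this size could not settle rare serious harms even with every count shown. Safety is not a stated primary or secondary objective either. All of this stands and lowers the severity. It does not justify withholding the counts, which readers need for description and for pooling with other studies.

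**Conclusion.** The concern holds in a limited form. As written, the suppression rule contradicts the commitment to report numbers of patients and events. If it is applied to harms tables, it would mask most non-zero counts of rare harms: 0.97 to 0.63 of them at assumed risks of 1% to 4% with 50 per arm, and somewhat more with 38. Harms affecting 10% or more would mostly still be shown. Dislocations are reportable adverse events with no stated class, and the class for acute severe pain is open to interpretation.

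The size rests on assumed risks and on the rule being used for harms, which the text permits but does not say. Severity is moderate to low. This is a reporting-rule correction; it does not touch the primary analysis, the data collected or the reporting of serious events to the ethics committee.

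**What to change.** - **Confidentiality {27}:** state that aggregate adverse event counts by randomised arm, of patients and of events and including zeros, are exempt from small-cell suppression, provided they are not cross-tabulated with personal characteristics.
- **Adverse event reporting and harms {22}:** state in which reported category dislocations and acute severe pain are counted, with patients and events given by arm. Naming the category is enough; a new harm class is not required, and nothing here calls for exempting outcome counts in general.

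The cost is two sentences, settled before the results are published and preferably before allocation is revealed. No data collection or clinical procedure changes. The downside is a very small disclosure risk from showing counts of one or two, which the bar on cross-tabulation limits.

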### Plans for collection, laboratory evaluation, and storage of biological specimens for genetic or molecular analysis in this trial/future use {33}

Not applicable, as no such samples will be collected.

## Statistical methods

### Statistical methods for primary and secondary outcomes {20a}

The primary analysis will be performed at the primary endpoint (end of the 16-week intervention period). We will prepare a statistical analysis plan and make it publicly available before any analyses commence [66], and report data by using the “CONSORT 2010 statement: updated guidelines for reporting parallel group randomised trials” [67]. All primary analyses will follow the intention-to-treat principle, i.e. all participants will be included in the analysis according to the group to which they were randomised, independent of compliance and withdrawals.

A multivariable linear regression model will be applied to assess the between-group difference in the change from baseline to the 16-week follow-up. The model will contain the primary outcome (change in WOSI total) as the dependent variable, and treatment group (HEAVY or LIGHT) as the main effect, after adjusting for baseline score, age, sex as covariates, and the clustering of physiotherapy clinic. For continuous secondary outcomes, a similar multivariable linear regression model will be applied. For comparison of binary outcomes, multivariable logistic regressions will be applied to estimate between-group difference in proportions at the 16-week follow-up, with outcomes as dependent variables, and treatment group as the main effect, after adjusting for baseline score, age, sex as covariates, and the clustering of physiotherapy clinic.

An alpha level of 0.05 (two-sided) will be considered as being statistically significant. The epidemiologist will be blinded to the allocated interventions for the analysis of the primary outcome. Results for the primary endpoint will undergo blinded interpretation presented in an author consensus statement signed by all authors. The consensus statement will present two versions of the interpretation, first assuming that intervention A is the intervention, and then assuming that intervention B is the intervention [68]. This signed consensus statement will be made publicly available prior to breaking the randomisation code and revealing group allocation. This is to reduce bias and promote transparency in the interpretation of the current findings before any publication procedures are initiated. We will use Stata (StataCorp. 2019. Stata Statistical Software: Release 16. College Station, TX: StataCorp LLC).

### Interim analyses {21b}

Besides the stopping rule defined under the sample size calculation, no other formal stopping guidelines or interim analyses are planned.

### Methods for additional analyses (e.g. subgroup analyses) {20b}

The per-protocol population is defined as participants who adhere to the protocol, defined by the following criteria for both groups: did attend two thirds (67%) or more of the 48 planned exercise sessions, both at supervised clinical sessions and home-based sessions (documented by the exercise logbook and weekly questionnaire); did not stop the intervention during the 16-week intervention period; and did not receive new, important interventions other than the assigned treatment in the follow-up period (e.g. no surgery, no steroid injection, or concomitant supervised exercise-based treatment for the shoulder).

### Methods in analysis to handle protocol non-adherence and any statistical methods to handle missing data {20c}

In the intention-to-treat and per-protocol analyses, missing data at follow-up will be accounted for by using a multiple imputation technique with age, sex, group allocation (masked), and baseline values as predictors. For sensitivity purposes, missing data will be imputed using a non-responder imputation, in which baseline values are carried forward [65]. The rationale builds on the assumption that participants who drop out will return to their baseline WOSI score [66].

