##### Secondary self-reported outcomes

Data from each of the four subscales (physical symptoms, sports/recreation/work, lifestyle, and emotion) from the WOSI questionnaire will be reported. Shoulder pain will be measured using the NPRS with numbers from 0 to 10 (“no pain” to “extreme pain”) [42]. The worst, least, and average pain level for the past week will be measured every week. Pain intensity before and after each exercise session will be measured [42]. Assessment of shoulder symptoms other than pain (instability, subluxation, laxity) will be measured in the same way as for shoulder pain by the NRS from 0 to 10 (“no symptoms” to “extreme symptoms”).

To evaluate whether a health condition impacts the patient’s ability to perform activities they nominate as important to them, the Patient-Specific Functional Scale (PSFS) [43] will be used. At baseline, the participant is asked to identify up to three important activities being difficult or impossible to perform due to symptoms. The participant provides a rating for each selected activity, on an 11-point ordinal scale ranging from 0 (“unable to perform activity”) to 10 (“able to perform activity at the same level as before the injury or problem”). During reassessments, the participant is prompted to re-rate the same activities. The average of up to three specific activity scores is recorded, and the range of possible scores is 0–10. Higher scores indicate less impairment.

Assessment of fatigue will be performed with the Checklist Individual Strength (CIS), the subscale of fatigue, which has shown good reliability and validity. The CIS subscale of fatigue consists of 8 items each scored on a 7-point Likert scale (scores ranging from 8 to 56) with high scores indicating high levels of fatigue [44].

To assess functional health status, the Dartmouth Primary Care Cooperative Research Network/World Organization of National Colleges, Academies and Academic Associations of General Practitioners/Family Physicians (COOP/WONCA) questionnaire will be used. The questionnaire is a generic health status questionnaire for general practice patients. The questionnaire consists of six single-item measures: physical fitness, feelings (mental well-being), daily activities, social activities, change in health, and overall health. The categories chosen are scored from 1 (good functional status) to 5 (poor functional status) with total scores ranging from 6 to 30 [45, 46].

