### Sample size {14}

Sample size calculation is based on the between-group difference in the mean change scores of WOSI total from baseline to the 16-week follow-up. Based on previous studies on patients with HSD/hEDS, we expect a mean baseline WOSI total of 1050 points [8, 22]. The study will be powered to detect a between-group difference equal to or greater than a previously reported clinically important change of 252 points [40, 63], with an SD for change from baseline to the 16-week follow-up of 350 points [16, 22]. We expect both groups to experience a clinically relevant improvement, seen as a 48% improvement in the HEAVY group (equal to 504 points with an expected baseline mean score of 1050 points) comparable with effects of previous interventions [16, 18, 22, 34, 64, 65] and 24% improvement in the LIGHT group [18] (equal to 252 points with an expected baseline mean score of 1050 points). With a two-sided significance level of 0.05 and 90% power, a sample size of 42 per group is required to detect a statistically significant difference. We decided to enrol 50 patients per group to account for a conservatively estimated dropout of 16% [16, 18]. If 100 patients are not included within 24 months (01 Apr 2019 to 31 Mar 2021), a stopping rule will be applied as soon as a minimum of 76 patients have been included, equal to a power of a minimum of 80%, including 16% dropout.

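### The imputation model uses almost only the primary model's own covariates and ignores the weekly symptom and session data, and baseline carried forward, the one sensitivity analysis named for missing WOSI, is not reliably conservative

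*Protocol article*

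**What the plan says.** Section {20c} of the protocol article says that missing follow-up data in both the intention-to-treat and the per-protocol analyses will be handled "by using a multiple imputation technique with age, sex, group allocation (masked), and baseline values as predictors". For sensitivity, "missing data will be imputed using a non-responder imputation, in which baseline values are carried forward", on the stated assumption that people who drop out return to their baseline WOSI. The only other sensitivity analysis, in the COVID-19 section, concerns delayed objective measurements and not missing WOSI scores.

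The primary model in section {20a} regresses change in WOSI on treatment group "after adjusting for baseline score, age, sex as covariates, and the clustering of physiotherapy clinic".

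Post-baseline information is plentiful. Under the secondary self-reported outcomes, "The worst, least, and average pain level for the past week will be measured every week", and other shoulder symptoms are rated in the same way. Section {11c} describes a weekly question on completed sessions for both groups, and section {18b} describes e-mail reminders and phone calls to people who do not answer.

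Section {14} plans for 16% dropout without splitting it by arm. It also states: "We expect both groups to experience a clinically relevant improvement", namely 504 points in HEAVY and 252 in LIGHT.

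**The concern.** Multiple imputation improves on dropping incomplete cases only if the imputation model holds something that the analysis model lacks, usually measurements taken after baseline. Here it holds nothing of the kind. The weekly ratings are natural predictors of both leaving the trial and the final WOSI, and they are already in the database. If symptoms drive people out of one arm and not the other, the named predictors cannot see it, and the primary estimate carries the bias.

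The reader would then rely on the sensitivity analysis. Baseline carried forward sets every missing participant to zero change. Because LIGHT is itself expected to improve, every LIGHT participant lost pulls the LIGHT mean down. Whether the analysis tests a HEAVY advantage or adds to it depends on who leaves, which nobody knows in advance.

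**Working it through.** **Inputs from section {14}.** Difference to detect 252 points ("a previously reported clinically important change of 252 points"); SD of change 350; mean improvement 504 (HEAVY) and 252 (LIGHT); 16% dropout; 50 enrolled per arm.

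**The plan's own figure.** Sample size per group = 2 × (1.960 + 1.282)² × (350/252)² = 40.5, so 41 by the normal formula. The t-test version gives 41.5, so 42, as stated. Then 42 / 0.84 = 50. The sample size reproduces and is not in dispute.

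**Step 1: planned imputation against complete cases.** In simulated trials (50 per arm, SD 350, 800 runs, 50 imputations, about 16% missing overall), the two estimates differed on average by at most 0.3 points. The SD of the difference was about 4 points, which is simulation noise, against a standard error of about 71.

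**Step 2: dropout related to the weekly course.** Three quantities are assumed because the documents do not give them: the dropout mechanism, the strength of dependence (odds ratio 2.7 to 4.5 per SD of the weekly score), and the correlation of the weekly score with WOSI change (0.5 to 0.7). The true difference is 252, with 16% missing in each arm.

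| Dropout | Planned imputation or complete case | Weekly score added |
|---|---|---|
| Symptom-driven in HEAVY only | about 275 to 299 | about 250 to 255 |
| Symptom-driven equally in both arms | about 250 to 255 | not needed |
| Completely at random | unbiased | unbiased; standard error falls from about 71.5 to 68.4–70.1 |

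The excess in the first row is 275 − 252 = 23 to 299 − 252 = 47 points. That is 9% to 19% of 252, or about 0.3 to 0.7 standard errors. With no true difference (both arms improving by 252, correlation 0.6), the same mechanism gave about 33 points in favour of HEAVY and a rejection rate of 7.9%, against 5.5% with full data.

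**Step 3: baseline carried forward.** Let m be an arm's mean improvement and d its dropout, with dropout unrelated to outcome. The estimated difference is m_H(1 − d_H) − m_L(1 − d_L). Only the 16% overall figure is in the protocol; the unequal splits are assumptions.

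| True state | HEAVY / LIGHT dropout | Calculation | Result | Truth |
|---|---|---|---|---|
| Planned effects | 16% / 16% | 504 × 0.84 − 252 × 0.84 | 211.7 | 252 |
| Planned effects | 10% / 22% | 504 × 0.90 − 252 × 0.78 | 257.0 | 252 |
| Planned effects | 8% / 24% | 504 × 0.92 − 252 × 0.76 | 272.2 | 252 |
| Both improve 252 | 10% / 22% | 252 × (0.90 − 0.78) | 30.2 | 0 |
| Both improve 252 | 8% / 24% | 252 × (0.92 − 0.76) | 40.3 | 0 |

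Under the planned effects the method overstates the difference once 252 × d_L exceeds 504 × d_H, that is, once LIGHT loses more than twice the proportion that HEAVY loses. With no true difference it favours HEAVY whenever LIGHT loses more. In the last row the simulated type I error was about 8%. If the losses are reversed, the bias goes against HEAVY.

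**Step 4: both together.** With equal dropout d, baseline carried forward is simply (1 − d) times the complete-case difference. For the HEAVY-only mechanism this gives 0.84 × 275 = 231 to 0.84 × 299 = 251, in line with the simulated 232 to 250. With no true difference it gives 0.84 × 33 = 28, and the simulation also gave 28. So it rescales the completers' difference and adds no information about those who left.

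**The case against.** Several parts of the opposing case stand.

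- A reader might infer that the planned analysis is biased towards HEAVY. The documents do not support that. The bias needs dropout that depends on symptoms differently by arm, and section {11b} applies the same symptom-modification rules to both. With symmetric or random dropout it vanishes.
- A reader might infer that baseline carried forward fails to test, or generally flatters, HEAVY. It does not in the planned case. Equal random dropout cuts 252 to 212, and HEAVY-only symptom-driven dropout gives 232 to 250, at or below the truth. At 10% versus 22% the overstatement under the planned effects is only 5 points.
- No dropout by arm is given. Section {6b} concedes far more supervised contact in HEAVY, so higher loss in LIGHT is plausible, but no more than that.
- Clinic is in the analysis model and absent from the imputation model. Without an intraclass correlation no consequence can be shown, so nothing is claimed for it.
- Imputing separately by arm from many weekly blocks would be heavy for about 42 completers per arm. Weekly answers may also stop when a participant leaves.
- Multiple imputation is valid if data are missing at random given the named predictors, and the promised analysis plan could widen the model. However, section {20c} names the predictors, so this is a choice already made and not a detail left open. The words on baseline values may cover other baseline scores, but those say nothing about the course after randomisation.

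**Conclusion.** The point holds in a limited form. As written, the imputation is in effect a complete-case regression when only the follow-up WOSI is missing, and it leaves aside data already collected in both arms that could protect the estimate. This first part follows from the two lists of terms and needs no assumption about dropout.

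The possible bias, about 23 to 47 points on a true 252, is conditional on arm-specific symptom-driven dropout of about 16% and on the assumed correlations and odds ratios. It is a risk to guard against and not an established error.

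Baseline carried forward is conservative under the planned effects unless LIGHT loses more than twice the proportion that HEAVY loses. It is not conservative where protection matters most: with no true difference it favours HEAVY when LIGHT loses more, and it keeps 84% of any selective-dropout bias when losses are equal at 16%. It should not stand as the only sensitivity analysis for missing WOSI.

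**What to change.** In section {20c}, and in the analysis plan before any analysis begins:

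1. Add a small set of auxiliary variables to the imputation model, for example the last available weekly average pain score, the last available weekly symptom score, and the number of completed sessions. Keep the primary analysis model unchanged.
2. Keep baseline carried forward if wanted, but supplement it with a delta-adjusted (tipping-point) analysis of the imputed WOSI values, with the shift varied separately in HEAVY and LIGHT, and report where the conclusion changes. With 16% imputed in one arm, a shift of δ in that arm moves the group difference by 0.16 × δ: 40.3 points for δ = 252 and 80.6 points for δ = 504. The range to be examined can therefore be fixed in advance.

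Cost: a slightly larger imputation model, one extra sensitivity analysis and a few lines of Stata. No new data are needed, and if dropout proves random nothing is lost.
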